### Sample size calculation

Accepting an alpha risk of 0.05 and a beta risk of less than 0.2 in a bilateral contrast, 21 subjects in the PU + TAU group and 21 in the WL + TAU group are needed to detect a difference equal to or greater than 1.57 units. The common standard deviation is assumed to be 1.6. A follow-up loss rate of 20% has been estimated.

### Data analysis

To analyze the improvements in primary and secondary variables throughout the study, linear mixed model analysis will be used. This analysis will allow us to study the main effects of time (pre-test, post-test, 3-month follow-up), treatment condition (TAU vs. TAU + UP), and number of sessions received (CBT sessions in TAU, UP sessions, etc.). We will also calculate interaction effects (e.g., treatment condition × time, or treatment condition × number of sessions × time, and the type and dosage of medication) which will reveal whether the treatment condition and the number of sessions received interacted with time in the prediction of changes in study outcomes. In the event that we observe a significant interaction, *post hoc* analysis will be conducted. Due to the nature of the present study, we expect to identify subgroups of patients presenting differing evolutions in study variables according to the number of sessions they have received.

The rate of transition to psychosis of patients in each condition and the CAARMS symptom severity will be calculated in order to evaluate changes in subthreshold psychotic symptoms (Morrison et al., 2012). We will also analyze the different clinical trajectories in the two groups following other previous studies (Polari et al., 2018). If any participant makes a transition to psychosis during their participation in the study, they will be excluded (full-blown psychosis is an exclusion criterion) and their data will be taken into account for further analysis. Finally, satisfaction of patients undergoing group treatment will also be analyzed.

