### Data collection

The evaluation is being carried out at 3 time points. A detailed description of the measures used in each evaluation is reported in Supplementary Appendix B.

Evaluators have been trained in psychological evaluation and specifically in the administration of the CAARMS (Yung et al., 2005). They also are blind to the condition of the study to which the participants have been assigned. In order to ensure internal consistency of the evaluations, interobserver reliability will be calculated with the Cohen kappa. At the beginning of each session with the group receiving UP, two scales are administered, the ODSIS and the OASIS, to measure the severity of depression and anxiety experienced during the previous week, in order to observe fluctuations during treatment. This procedure is performed following the recommendations of the UP manual (Barlow et al., 2019).

CAARMS scores are also collected at the time patients begin treatment in our early psychosis program, prior to entering the baseline assessment of the present study. Medication changes and number or TAU sessions will be recorded as a control variables. Types and dosages of medication will be recorded at the three time points of assessment.

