### Interventions

All study participants receive TAU, within our early intervention program. It includes the following interventions: psychological therapy (about 20–40 sessions of CBT) as well as psychiatric treatment (with antidepressants, benzodiazepines and only when needed antipsychotic medication), social work intervention (vocational orientation and support), nursing care (side effects monitoring and healthy habits), individual cognitive remediation (if necessary), and family therapy. The number of sessions received in TAU depends on the clinical status of each patient. The maximum duration of TAU is 5 years. CBT delivered in TAU consists of techniques such as behavioral experiments, socratic questioning, and some exposure techniques mainly focused on subthreshold psychotic symptoms (French and Morrison, 2004; Nelson and Orygen Youth Health Research Centre Issuing Body, 2012; Van der Gaag et al., 2013a). Patients receive weekly or fortnightly sessions of psychotherapy. UP includes establishment of the specific therapeutic aims of each participant, motivation techniques, emotional psychoeducation, teaching functional analysis of the emotional experiences, mindfulness techniques, cognitive flexibility, analysis of emotional behaviors, and training in opposite behaviors. We also use interoceptive exposure, which we never use in individual CBT, and we teach patients to create exposure hierarchies for intense emotions so that they can follow treatment without the continuous supervision of a therapist. The UP consists of 15 online group sessions of 2 h each week. The groups include 5–8 participants. Participants receive an additional follow-up session 1 and 3 months after the end of the program. The sessions work on the 8 modules of UP for the transdiagnostic treatment of emotional disorders, as detailed in the reference manuals (Barlow et al., 2019). A summary of each session of the UP is detailed in Supplementary Appendix C.

Fidelity to the UP treatment protocol is guaranteed through weekly supervision with an accredited therapist. In addition, the therapists who will perform the UP intervention have undergone a 20-h training course. The contents of each module are summarized in an infographic and delivered to patients after the UP session to improve adherence to the intervention and acquisition of the techniques.

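### The efficacy mixed model brings in post-randomisation session counts and medication, and no primary condition × time contrast free of them is named

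*Protocol article*

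**What the plan says.** The Data analysis section assigns a linear mixed model to the primary and secondary variables. Its main effects are time, "treatment condition (TAU vs. TAU + UP), and number of sessions received (CBT sessions in TAU, UP sessions, etc". The interactions are given as examples: condition × time, or "treatment condition × number of sessions × time, and the type and dosage of medication". The section adds that "we expect to identify subgroups of patients presenting differing evolutions in study variables according to the number of sessions they have received".

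Other sections show that these terms are meant as adjustment:

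- Data collection: "Medication changes and number or TAU sessions will be recorded as a control variables". Medication type and dose are recorded at all three assessments, two of which follow randomisation.
- Interventions: service use under TAU is counted in both arms so that the analyses can allow for it. The same section says "The number of sessions received in TAU depends on the clinical status of each patient".
- Discussion: the authors count on these analyses to overcome the difficulty of isolating what UP contributes.

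Under Study design, waiting-list patients are offered UP only after the final assessment. Under Study aims, the main objective is UP added to TAU against TAU alone, for anxiety and depression.

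**The concern.** The main objective is a randomised comparison. Sessions and medication used after randomisation are not baseline characteristics and can be consequences of the assigned arm and of the outcome. If UP relieves symptoms, a patient may need fewer TAU sessions or less antidepressant or benzodiazepine treatment. Holding those quantities fixed removes part of the UP effect and brings in confounding by indication.

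The UP session count has a further problem: it is zero for every control, so it nearly copies the arm indicator. Subgroups formed by sessions received compare attenders with non-attenders, not randomised groups.

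At stake is whether the reported treatment effect answers the trial's question. In a trial of 42 patients, an effective UP could appear weak or absent, and an apparent dose-response could reflect severity or adherence.

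**Working it through.** **The plan's own figure.** The Sample size section sets two-sided alpha 0.05 and power of at least 0.80, and says "21 subjects in the PU + TAU group and 21 in the WL + TAU group are needed". The target effect is 1.57, with SD 1.6 and 20% loss. The formula n = 2 × [1.6 × (1.960 + 0.842) / 1.57]² gives 16.3, so 17 per arm. Dividing by 0.8 gives 16.3 / 0.8 = 20.4, so 21 per arm. The figure reproduces and is not in question. The 17 completers per arm used below are that n before inflation.

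**Identifiability (no assumption needed).** Let G be arm (0/1), U the UP session count, and t1, t2 the two later visits. U = 0 whenever G = 0, so G × U = U for every patient. The full three-way model has 12 columns: 1, t1, t2, G, U, G·t1, G·t2, U·t1, U·t2, G·U, G·U·t1, G·U·t2. The last three duplicate U, U·t1 and U·t2, so the rank is 12 - 3 = 9. Without them the model has 9 columns and rank 9 when attendance varies. If every UP patient attended all 15 sessions, U = 15 × G, and arm and UP count could not be separated (rank 2 of 3 with the intercept).

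**Session count as a main effect only.** A per-patient total that is constant over visits shifts all of that patient's visits equally. With complete data, the within-patient change, and so condition × time, is unaffected. Harm starts when sessions × time enters; the three-way term brings it in.

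**TAU sessions × time.** Assumed inputs: effect -1.57 and SD 1.6 (from the plan); pre-post correlation 0.5; TAU count S = post-treatment score plus noise, with pooled correlation ρ between S and the score.

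- With complete data, condition × time at post-treatment is the arm difference in change D. The SD of D is 1.6 × √(2 × (1 - 0.5)) = 1.6.
- Within arm, Cov(D, post) = 2.56 × (1 - 0.5) = 1.28.
- The pooled variance of the post score is 2.56 + 1.57² / 4 = 3.176.
- The adjusted effect is -1.57 × (1 - k), where k = 1.28 / [2.56 + 3.176 × (1/ρ² - 1)].

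| ρ | k | by formula | by simulation |
|---|---|---|---|
| 0.3 | 0.037 | -1.51 | -1.52 |
| 0.5 | 0.106 | -1.40 | -1.40 |
| 0.7 | 0.218 | -1.23 | -1.23 |

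**UP sessions × time.** Assumed attendance: mean 12, SD 3, capped at 15. The condition × time coefficient is now the UP-arm regression line read at zero sessions, minus the control mean.

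- If benefit is proportional to attendance, the effect at zero sessions is 0. The expected estimate is therefore 0, with a rejection rate of about 0.05.
- If benefit does not depend on attendance, the estimate stays near -1.57. Its variance is 2.56 × [2/17 + 12² / (16 × s²)]. For s = 3 this is 2.56 × (0.118 + 1.000) = 2.86, so SE 1.69 and power about 0.15. For s = 2.5 it is 2.56 × (0.118 + 1.440) = 3.99, so SE 2.00 and power about 0.12. The cap at 15 reduces the spread below 3, and simulation gives power of about 0.13.
- For comparison, without session terms the SE is 1.6 × √(2/17) = 0.55 and power is about 0.79 by t test.

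**The case against.** The strongest reply is that the article does not write down a single joint model. It says which effects the method allows the authors to study, and it gives the interactions as examples joined by an or. Condition × time comes first and contains no session term. If each term were fitted separately, that contrast would be intact, and a fuller plan may say so. This stands as a limit: the text does not prove that the randomised contrast will be distorted. It does not dispose of the point, because Data collection, Interventions and the Discussion all present sessions and medication as adjustment for the treatment comparison, and the article does not mark an unadjusted contrast as primary.

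A reader might infer that the treatment effect as planned cannot be estimated at all. The documents do not support that. Non-identifiability is confined to the condition × UP-session terms, or to uniform attendance. TAU sessions and medication can be non-zero in both arms, and there the problem is bias.

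A reader might also infer that any session term biases the result. A time-constant main effect leaves condition × time alone with complete data. Regressing the post-treatment score on arm, baseline and sessions would give larger TAU-session bias, but that is not the repeated-measures model planned here.

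Two further points stand. The article does not define the window over which TAU sessions are counted, and sessions before baseline would be a legitimate covariate. The strength of the session-severity link is not given anywhere.

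**Conclusion.** The concern holds in this form: the stated analysis lets post-randomisation session counts and medication into the model used to judge efficacy, and it names no primary contrast free of them. The identifiability result follows from the design alone.

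The sizes are conditional on the assumed inputs. For TAU sessions × time the loss is modest to material: -1.57 becomes -1.52 to -1.23, roughly 3% to 22% smaller (0.05/1.57 to 0.34/1.57). For UP sessions × time it is decisive either way: an estimate near 0, or power of about 0.13 against about 0.79. These figures assume complete data on 17 per arm, a pre-post correlation of 0.5, and in-trial TAU counts that follow concurrent severity. The effect of adjusting for medication was not quantified. The argument there is qualitative: treatments that are part of TAU can change in response to the symptoms being measured.

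**What to change.** In the Data analysis section, name as primary the condition × time contrast from a mixed model with randomised arm, time and arm × time. Allow only pre-randomisation covariates, such as baseline medication and TAU sessions received before baseline. Revise the control-variable wording in Data collection and the matching sentence in Interventions to agree.

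Report in-trial sessions and medication descriptively by arm. Label every session or medication interaction, dose-response analysis and session-defined subgroup as exploratory. Study UP dose-response within the UP arm, or by a complier analysis that uses randomisation as the instrument. Drop condition × UP sessions (× time), which cannot be identified.

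The cost is a change of wording, with no new data, patients or sample size. The downside is that questions about sessions and dose become exploratory, and the Discussion can no longer rely on them to isolate the effect of UP.

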### Study aims

Given the high level of comorbid anxiety and depression among individuals meeting UHR criteria, the main objective of our study is to evaluate the efficacy of UP in addition to TAU as compared to TAU in targeting symptoms of anxiety and depression in UHR for psychosis patients.

As secondary objectives, changes in attenuated symptoms of psychosis, transition to psychosis rates, cognitive distortions, quality of life, metacognition, personality, and psychosocial functioning, and the satisfaction of participants with the treatment, are being assessed. Further, assessment will be made of whether the results are maintained at 3 months’ follow-up. Different clinical trajectories will be analyzed for comparison with previous studies (Polari et al., 2018).

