Given the high comorbidity of emotional disorders in patients with UHR (Rutigliano et al., 2016) and the presence of errors in information processing in both groups of disorders, such as jumping to conclusion, selective care, and catastrophization, as well as avoidant behaviors (Livet et al., 2020), it is likely that these share common transdiagnostic mechanisms with ED. It may be the case that improving emotional regulation will have a positive effect on cognitive biases implicated in the onset and maintenance of both emotional disorders and symptoms of psychosis. If the results show positive associations between improved emotional regulation and improvement in cognitive biases, this would provide a strong theoretical and clinical basis for offering UP to people at the UHR of psychosis.

One limitation of the study is the potential difficulty in isolating the impact of UP on outcome measures. This study is a naturalistic study, that is, it is carried out in the context of public mental health, which is why it is comparable with what has been done up to now. Clinically, it would be more ethical to offer an intervention like UP to all the participants of the study. We expect that the statistical analyses mentioned above can increase the robustness of the study results and solve this limitation.

The UP has already been shown to be effective with similar symptoms (Sakiris and Berle, 2019; Cassiello-Robbins et al., 2020; Carlucci et al., 2021) and this brings us closer to the clinical reality of mental health services for young people in public health. Furthermore, this design may make it easier to collect more samples since this type of patient is not very prevalent. There are several previous studies that have used this type of methodology (e.g., Carl et al., 2014). In this sense, this would be the first step toward obtaining preliminary data on whether the UP adds something to what is already done and to assess aspects of viability and user satisfaction. The next steps will be to compare the UP in isolation with the TAU.

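### Follow-up comparisons depend on a significant interaction, and no between-arm contrast at a named visit is promised whatever that test shows, although the sample size rests on one such contrast

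*Protocol article*

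**What the plan says.** All references are to the protocol article.

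- **Study aims.** The objective is a between-arm one: "the main objective of our study is to evaluate the efficacy of UP in addition to TAU as compared to TAU", on anxiety and depression. Whether results persist at 3 months is a further aim.
- **Sample size calculation.** The basis is a plain two-group comparison: "Accepting an alpha risk of 0.05 and a beta risk of less than 0.2 in a bilateral contrast", with "21 subjects in the PU + TAU group and 21 in the WL + TAU group are needed" for a difference of at least 1.57 units. "The common standard deviation is assumed to be 1.6", and "A follow-up loss rate of 20% has been estimated".
- **Data analysis.** A linear mixed model studies main effects of time (three visits), condition and number of sessions. It also calculates interactions, with condition by time and condition by sessions by time as examples, and medication is mentioned too. None of these is conditional. Post hoc analysis is: it follows "In the event that we observe a significant interaction". The section does not say which interaction is the trigger or which comparisons the post hoc step contains.
- **Discussion.** The trial's purpose is modest: "this would be the first step toward obtaining preliminary data on whether the UP adds something to what is already done".

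**The concern.** The section writes down a rule. Its ordinary reading is that the arms are compared visit by visit only after the overall condition-by-time test reaches significance. The test that decides is then a 2-df test over three visits, while the trial was sized for a 1-df difference between two means.

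Two things would follow. Power for the comparison of interest is lost, because two tests must succeed instead of one. And the visit-level estimate, when it is presented as a follow-up result, has been selected on significance and so tends to be too large. For a small trial meant to supply preliminary data, the estimate of added benefit with its interval is the main product, and this rule leaves its reporting to chance.

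**Working it through.** **1. The plan's own figure.** Inputs from the Sample size calculation: difference 1.57, SD 1.6, two-sided alpha 0.05, power 0.80.

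n per arm = 2 × (1.960 + 0.842)² × (1.6/1.57)² = 16.3, so 17. Allowing for 20% loss: 16.3/0.8 = 20.4, so 21. The stated 21 reproduces. After the loss, 21 × 0.8 = 16.8, about 17 per arm. Power at 17 is 0.82 (normal approximation) or 0.79 (t). The calculation is therefore for one 1-df contrast at one time.

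**2. Can the unconditional terms stand in for that contrast?**

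- Condition main effect, averaged over visits: with no difference at baseline and 1.57 held afterwards, (0 + 1.57 + 1.57)/3 = 1.05. If the effect halves by 3 months, (0 + 1.57 + 0.785)/3 = 0.785. This is not the quantity in the sample size.
- Condition by time: a 2-df test giving one p-value, with no named visit.

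**3. How often the trigger opens.** Assumptions not in the document: compound symmetry, complete data, no session or medication terms, and correlation ρ of 0.3, 0.5 or 0.7. The F test has 2 and 64 df and noncentrality λ = (n/2) × Σ(d_t − d̄)² / [σ²(1 − ρ)], where d_t is the arm difference at visit t.

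- Held: Σ = (2/3) × 1.57² = 1.643. At ρ = 0.5, λ = 8.5 × 1.643/(2.56 × 0.5) = 10.9.
- Halved: Σ = 2 × 0.785² = 1.232. At ρ = 0.5, λ = 8.5 × 1.232/1.28 = 8.2.

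Simulation (20,000 runs or more per scenario) gives the opening rates below and, for the baseline-adjusted post-test contrast, the power alone and the power when the trigger must also open.

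| True 1.57, 17 per arm | ρ = 0.3 | ρ = 0.5 | ρ = 0.7 |
|---|---|---|---|
| Contrast alone | 0.82 | 0.88 | 0.97 |
| Trigger opens, held | 0.68 | 0.83 | 0.97 |
| Contrast behind trigger, held | 0.61 | 0.78 | 0.95 |
| Trigger opens, halved | 0.55 | 0.71 | 0.91 |
| Contrast behind trigger, halved | 0.53 | 0.69 | 0.90 |

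With all 21 per arm retained, the contrast alone has power 0.89, 0.94 and 0.99. Behind the trigger it has 0.73, 0.87 and 0.98 (held) or 0.63, 0.79 and 0.96 (halved).

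**4. Size of the selected estimate.** Mean baseline-adjusted estimate among trials that pass the trigger, 17 per arm:

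| | ρ = 0.3 | ρ = 0.5 | ρ = 0.7 |
|---|---|---|---|
| True 1.57, held | 1.71 (+9%) | 1.66 (+6%) | 1.59 (+1%) |
| True 1.57, halved | 1.85 (+18%) | 1.76 (+12%) | 1.63 (+4%) |
| True 0.8 (assumed, 0.5 SD), held | 1.16 (+45%) | 1.13 (+41%) | 1.03 (+29%) |

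In the 0.8 case the trigger opens in about 22%, 29% and 46% of trials.

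**5. Type I error.** With no true effect, the trigger and the post-test contrast are both significant in about 1.5% to 2.7% of trials (baseline-adjusted or change-score contrast). The rule is conservative for this contrast.

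**The case against.** The strongest reply is that the trial always yields between-arm results. The condition main effect and the condition-by-time interaction are calculated whatever happens, and with three visits the interaction coefficients are themselves the differences in change at post-test and at 3 months. Nothing forbids reporting them. This stands. A reader might infer that the trial could report no between-arm effect at all, or hold no estimate of one; the article does not support that. What is missing is a commitment to report one visit-level contrast with its interval regardless.

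Second, the content of the post hoc step is inferred. The same paragraph covers interactions with session number and medication, and goes on to expect subgroups defined by sessions received, so the step could mean probing those. This also stands: visit-level arm comparison is the usual sequel to a condition-by-time interaction, but it is not stated.

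Third, the power loss depends on the comparator. At correlation 0.5 with the effect held, the trigger opens in about 83% of trials, while an unconditional raw change-score contrast reaches significance in about 80%. Setting a 71% opening rate against the planned 80% requires the effect to halve, which the article does not predict; its Introduction cites maintained benefit. Likewise, an exaggeration of 1.6 times arises only for raw change scores at about half the design effect (1.30/0.8 at correlation 0.5). Neither figure is a fair headline. The loss remains against a baseline-adjusted contrast, even with the effect held.

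Fourth, a condensed article may leave the deciding contrast to an analysis plan. That would answer a silence. Here a conditional rule is stated, and a later plan would have to depart from it.

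**Conclusion.** The point holds in limited form. The Data analysis section ties follow-up comparisons to a significant interaction and promises no arm contrast at a named visit outside that step, while the sample size assumes exactly such a contrast. The two unconditional terms do not replace it.

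At the design effect with 17 per arm, the cost in power runs from about 2 percentage points (correlation 0.7, held) to about 29 (correlation 0.3, halved). Upward bias in estimates that pass runs from 1% to 18%, and is larger for smaller true effects. At high correlation with a sustained effect the harm is slight. These sizes rest on assumed correlations, compound symmetry, complete data and the ordinary reading of the post hoc step. The mismatch between the stated rule and the sample size does not depend on the correlations or the simulation.

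The rule does not raise the false-positive rate, and it does not leave the trial without any between-arm result.

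**What to change.** In the Data analysis section, replace the conditional sentence with wording to this effect:

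- The between-arm difference at post-test and at 3 months is estimated from the mixed model, adjusted for baseline, and reported with a 95% confidence interval whatever the interaction p-value.
- The 1-df post-test contrast, which matches the sample size calculation, is the test of the main objective.
- The overall condition-by-time test is supportive. Any further post hoc analysis is labelled exploratory, with the interaction that prompts it named.

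The cost is two or three sentences. No new data, visits or patients are needed, since the same fitted model supplies both contrasts. The change should be dated before the between-arm data are examined.

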### Participants

Participants are people who meet criteria of UHR for psychosis and who have comorbid symptoms of emotional disorders and are receiving treatment in one of the Early Pychosis Programs (PIPPEP) in Parc Sanitari Sant Joan de Déu.

The inclusion criteria are (1) age between 18 and 35 years old, (2) a diagnosis of UHR for psychosis in the last 3 years and inclusion in our early intervention program, (3) symptoms of a comorbid emotional disorder, (4) fluent Spanish or Catalan, and (5) signing the informed consent (IC).

The exclusion criteria are (1) a frank psychotic episode in the past or in the present, (2) intellectual disability, (3) an organic disorder that explains current symptomatology.

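### The rule for participants who transition to psychosis does not say what they are excluded from, and if it ends assessments or analysis, an outcome decides which data are compared

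*Protocol article*

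**What the plan says.** All of the following is in the protocol article.

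- **Participants.** One of the exclusion criteria is "a frank psychotic episode in the past or in the present". It is listed as a condition for entry.
- **Study aims.** The secondary objectives include "changes in attenuated symptoms of psychosis, transition to psychosis rates".
- **Data analysis, by-arm reporting.** "The rate of transition to psychosis of patients in each condition and the CAARMS symptom severity will be calculated". The section also plans to compare clinical trajectories between the two groups.
- **Data analysis, handling rule.** The trigger is "If any participant makes a transition to psychosis during their participation in the study". The consequence is that "they will be excluded (full-blown psychosis is an exclusion criterion) and their data will be taken into account for further analysis".
- **Data analysis, model.** For primary and secondary variables, "linear mixed model analysis will be used", with three time points: baseline, post-treatment and 3-month follow-up.

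The article contains no intention-to-treat statement or other sentence that settles what exclusion means here.

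**The concern.** The rule takes a criterion for entry and applies it to an event after randomisation, and that event is one of the trial's own outcomes. Randomisation protects the comparison only while membership of the compared groups, and the collection of their data, do not depend on what happens later. Participants who transition are likely to be among those with the worst course. If their later scores are missing or dropped, the arm with more transitions looks better on the continuous outcomes than it should.

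The main comparison of anxiety and depression is exposed, as are functioning and CAARMS severity. CAARMS severity is the most exposed, because the courses cut short are those with the most severe psychotic symptoms. Assessments that were never made cannot be recovered at the analysis stage.

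**Working it through.** **1. What exclusion could mean**

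| Reading | Consequence for the data | Fit with the rest of the text |
|---|---|---|
| Leaves study treatment only | All assessments and analyses continue; no problem | Possible, but not stated |
| Leaves the study, data already collected are kept | Later assessments are missing because of an outcome | Fits the second half of the sentence, the rate per condition and the trajectory comparison |
| Removed from analysis | The analysis set depends on an outcome | Fits worst: the same sentence says the data will be used, and a rate per condition needs these participants counted |

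The middle reading is the most natural. With three time points, someone who transitions before the post-treatment assessment then contributes a baseline score only. Someone who transitions later lacks the follow-up score. A linear mixed model uses such partial records, but it corrects for the missing scores only as far as they are predictable from the observed ones.

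**2. The plan's own figure**

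Inputs from Sample size calculation: two-sided alpha 0.05, power at least 0.80, difference 1.57, SD 1.6, loss 20%, 21 per arm.

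- n per arm = 2 × [1.6 × (1.960 + 0.842) / 1.57]² = 16.3
- 16.3 / 0.8 = 20.4, rounded up to 21

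The stated 21 per arm reproduces and is not in dispute. No expected transition rate is given, and no separate allowance for excluded participants is stated.

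**3. Illustration of the shift, on assumptions only**

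Assume that k of the 21 participants in one arm transition and nobody in the other does, that they score d worse than the rest of their arm, and that all their data are deleted. That arm's mean then improves by k × d / 21. Take d as 1 to 2 SD, that is 1.6 to 3.2 units.

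| k | d = 1.6 | d = 3.2 | Share of 1.57 |
|---|---|---|---|
| 0 | 0 | 0 | 0% |
| 2 | 2/21 × 1.6 = 0.15 | 2/21 × 3.2 = 0.30 | 10 to 19% |
| 3 | 3/21 × 1.6 = 0.23 | 3/21 × 3.2 = 0.46 | 15 to 29% |

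If transitions occur in both arms, the shift is (difference in transition proportions) × d. For an assumed 10% against 5% with d = 1.6, it is 0.05 × 1.6 = 0.08. For 20% against 5% with d = 3.2, it is 0.15 × 3.2 = 0.48. These are 5% and 31% of 1.57.

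**4. Direction**

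Deleting worse-scoring participants improves the mean of the arm they leave. If more controls transition, the apparent benefit of UP shrinks. If more UP participants transition, UP looks better on the continuous outcomes than it should.

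**The case against.** The strongest reply is that the two halves of the sentence belong together: the person leaves the study and the data are kept. Read so, the sentence does not contradict itself. The by-arm transition rate and the trajectory comparison support this, since the Introduction describes earlier trajectory work as covering courses up to and including transition. This stands. A reader might infer that the plan certainly deletes these participants from the analysis set; the text does not establish that. It also does not say outright that assessments stop.

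A reader might also infer that the rule could hide harm from UP altogether. It could not, because an excess of transitions under UP would appear in the rate per condition. Only the continuous outcomes could mask it.

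The illustration is open to challenge as well:

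- The one-sided counts and the gap of 1 to 2 SD are assumptions, and the article does not name the scale behind 1.57 and 1.6.
- It supposes full deletion, which the sentence seems to rule out.
- Two or three of 21 (10 to 14%) could fall within the 20% loss already allowed, so an additional loss of power cannot be claimed.

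All three stand and limit the figures to an order of magnitude.

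Finally, definitions of analysis sets are commonly left to an analysis plan. That does not dispose of the point, because the article itself states a rule and leaves its meaning open.

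**Conclusion.** The point holds as an unresolved rule that can bias the comparison. It does not hold as a proven removal of randomised participants. On the most natural reading the consequence is missing follow-up that depends on an outcome; on the harsher reading it is an outcome-dependent analysis set. Both favour the arm with more transitions, provided that those who transition score worse.

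The documents do not allow the size to be derived. The range of 0.15 to 0.46 units applies only if 2 to 3 participants in one arm and none in the other transition, score 1 to 2 SD worse and have all their data deleted. Few participants are likely to be affected, but in a trial of 42 a few are enough to matter.

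**What to change.** Replace the sentence in Data analysis with: *Transition is an outcome; participants who transition remain in their randomised arm and in all analyses, and are invited to the remaining scheduled assessments.*

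In addition:

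- count transitions over all randomised participants in each arm;
- add a sensitivity analysis of the primary outcome that uses data up to transition only.

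The criterion in Participants stays as an entry rule. Which treatment a participant receives after transition is not touched by this change.

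The cost is the wording of an amendment and the completion of already scheduled assessments for a few participants. The change should be made while those assessments can still be collected.
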